## Abstract

**Introduction:**

In the Netherlands, approximately 2200 major amputations of the lower extremities are performed each year, the majority in vascular patients. Around 61% of these patients will develop postamputation pain (PAP). PAP is a severe, lifelong, disabling condition profoundly affecting quality of life. During amputations, the common practice is to cut the nerves without employing nerve-surgical techniques to prevent chronic pain due to neuroma formation. In recent years, targeted muscle reinnervation (TMR) has been the most frequently studied technique for treating PAP, inhibiting neuroma formation by rerouting the cut mixed nerve to a functional motor nerve. We hypothesise that a primary TMR procedure during major lower limb amputations will result in a lower prevalence of PAP.

**Methods and analysis:**

We propose a national, multicentre, randomised, sham-controlled trial comparing TMR with traction neurectomy in major amputations of the lower extremities in patients with vascular disease. 203 patients will be recruited with an indication for a transfemoral to transtibial amputation as a primary or secondary sequela of vascular disease. The subjects are randomly assigned to the TMR group or the traction neurectomy group. PAP will be evaluated 1 year postoperatively as the primary endpoint. Secondary outcomes include quality of life, mobility, neuropathic pain, hospital anxiety and depression, cost-effectiveness and complications.

**Ethics and dissemination:**

This study has been reviewed and approved by the local ethical review body, ‘The Medical Ethics Committee Leiden The Hague Delft’, under the reference: P24.073 on 28 November 2024. Results will be published in peer-reviewed journals.

**Trial registration number:**

NCT06719245. Dutch trial registry: NL87196.058.24

STRENGTHS AND LIMITATIONS OF THIS STUDYThe multicentre, randomised, sham-controlled design minimises potential bias.The study is appropriately powered to detect differences in both phantom limb pain and residual limb pain.The use of multiple validated questionnaires, including patient-reported outcome measures, ensures robust assessment of the treatment effect.The expected inclusion is limited to 40% of eligible patients due to the availability of nerve surgeons and the additional operating time in a semiacute setting.

## Introduction

### Background and rationale

 Approximately 2200 major lower extremity amputations, transfemoral to transtibial, are performed in the Netherlands each year, and the incidence is rising, particularly due to vascular disease.^1 2^ Around 61% of these patients develop postamputation pain (PAP).^3^ PAP is known to compromise prosthetic rehabilitation and profoundly diminish the quality of life after amputation.^4^ Patients with chronic pain report a lower health-related quality of life when a neuropathic component is present (0.70 vs 0.47).^5^ Moreover, it is associated with a significant burden on the healthcare system.^6^ Direct healthcare costs may comprise prehospital care, emergency care, hospitalisation, long-term postdischarge care and rehabilitation (eg, increased opioid use and other (neuropathic) pain medication and interventions by pain specialists to treat PAP). Indirect costs may arise as a consequence of loss of productivity for both patients and their families.

PAP falls into two major categories: residual limb pain (RLP, ‘stump pain’) and phantom limb pain (PLP). RLP has different aetiologies, including infection, vascular insufficiency, scar tissue, bone spurs and neuroma formation.^7^ PLP is caused by transection of the nerves during amputation. While the exact mechanism behind PLP is not yet fully understood, it is partly explained by deafferentation from the distal target. Currently, there is no uniform protocol for the surgical handling of nerves during amputations. There is little attention for nerve handling in surgical textbooks, the Dutch Guideline ‘Amputation and prosthetics of the lower extremity’ and the Global Vascular Guideline on the Management of Chronic Limb-Threatening Ischaemia do not mention nerve handling during amputation surgery.^4 8^ Today, techniques used depend primarily on traditions and expert opinions, which lack a solid scientific base. Nerve handling is performed with sharp transection or electrocautery, often using light traction or ligation. After the nerve is cut, it may be tucked away, coagulated, infiltrated with a local anaesthetic or alcohol or it may be left untreated.^9^

When PAP develops, it is very challenging to treat.^10^ If non-surgical treatments fail or side effects of medication dominate a patient’s life, surgery for PAP may be performed. Nerve-surgical techniques that are then applied differ widely and, again, lack any solid scientific base. In general, secondary surgery for PAP includes resection of the neuroma and translocation of the freshened nerve into surrounding tissue, such as muscle, bone or fat, or more advanced techniques like targeted muscle reinnervation (TMR), regenerative peripheral nerve interface or nerve capping.^11^,^13^

Several cohort studies and a recent randomised trial show that the nerve-surgical technique TMR is effective in the reduction of PAP, with limited complications and improved quality of life.^14^,^16^ As persistent nociceptive stimulation in chronic pain may cause various changes in pain physiology, leading to pain sensitisation, preventing this chronic pain syndrome might gain even larger benefits. Few small non-randomised cohort studies are published on primary TMR during or shortly after amputations.^17^,^23^ Despite issues with the validity of the articles, results were consistently in favour of primary TMR relative to standard neurectomy regarding all outcome measures, including intensity and interference with daily activities. Although the pooled estimates in the meta-analysis should be interpreted with great caution because of between-study heterogeneity, the risk of RLP and PLP may be halved when performing TMR.

Moreover, Deeyor *et al*^18^ calculated the 1-year healthcare cost in patients undergoing standard amputation and in those receiving an amputation with primary TMR. The average healthcare costs for the primary TMR group were $32 632 versus $36 219 for those receiving standard care (Phoenix, USA), supporting the cost-effectiveness of the intervention.^18^

The main drawbacks of TMR are that it is a nerve-surgical technique not routinely performed by amputation surgeons and that it is a time-consuming procedure, which might be cumbersome, especially in the semiacute setting of amputation surgery.

### Objective and hypothesis

In this study, we aim to compare primary TMR with traction neurectomy during a transfemoral to transtibial amputation as a primary or secondary sequela of vascular disease. We hypothesise that primary TMR will decrease PAP and improve quality of life at lower costs.

## Methods

### Study design

The PreventPAP trial investigators propose a national, multicentre, randomised, single-blind, sham-controlled trial comparing primary TMR with traction neurectomy in patients who undergo transtibial to transfemoral amputations as a primary or secondary sequela of vascular disease. The protocol is developed in accordance with the Standard Protocol Items: Recommendations for Interventional Trials guidelines.^24^ A summary of the trial information is presented according to the WHO Trial Registration Data Set (online supplemental file 1).

### Study population

The study population includes patients who receive a major amputation of the lower extremities as a primary or secondary sequela of vascular disease. To ensure a homogenous cohort, only patients with an amputation as a result of vascular pathology are included. In the Netherlands, this group accounts for 90%–95% of all amputations of the lower extremities.^4^ Moreover, as age above 75 years is a major risk factor for 1-year mortality, this group was excluded.^25^

Inclusion criteria

Patients aged between 18 and 75 years.Scheduled for a transtibial, through-knee or transfemoral amputation as a primary or secondary sequela of vascular disease.

Exclusion criteria

Insensate limbs at the level of amputation.Complex Regional Pain Syndrome.Existing neuroma or prior neuroma surgery in the affected limb.Undergoing radiotherapy on the affected limb.Cognitive impairment or delirium at the time of consent.Patients who are unfit for general anaesthesia.No nerve surgeon trained in the TMR procedure is available.

### Recruitment and consent

203 patients undergoing a major lower limb amputation will be randomised into two equal parallel groups after informed consent is given. One group will receive TMR, and the other group will receive traction neurectomy. Patients will be recruited from academic and non-academic hospitals in the Netherlands via the emergency department, ward or the outpatient clinic. After the indication for amputation is set, eligibility for inclusion is evaluated by the treating physician. Afterwards, the physician will contact an authorised local investigator to discuss the trial, obtain written informed consent (online supplemental file 2) and randomise the patient.

Patients who have undergone a major leg amputation and were not included in the trial will be consented for a parallel prospective registry study. This registry study is part of the PreventPAP trial and will be used as external validation and to enhance the interpretation of the trial results. Including all patients undergoing amputation could expose selection bias and make this study more pragmatic. In this study, we plan to report the same baseline, intraoperative and postoperative variables, and we will send the same questionnaires at 12 months, except for the cost-effectiveness questionnaires. This allows us to compare the outcome between the randomised and non-randomised groups, providing additional context and validation of the trial results.

### Study procedures

After randomisation, patients will receive general anaesthesia without a muscle relaxant for the TMR group. Intraoperative epidural anaesthesia is not allowed as this will reduce nerve conduction, making nerve stimulation less dependable. The amputation will be performed by a qualified vascular surgeon or a senior resident in training under supervision. The skin will be incised using a fishmouth incision (transfemoral and through-knee) and according to Burgess’ technique (transtibial). If patients are randomised in the TMR group, a trained nerve surgeon will perform the nerve coaptation. Postoperative protocol is similar for both interventions, including the use of analgesia. In transfemoral and through-knee amputations, there will be an additional 10-centimetre incision on the posterior side of the leg. This additional incision is necessary to coaptate the sciatic nerve. To ensure proper blinding, a sham skin incision will be performed in the control group. Closure and dressing of the wound will be similar between groups.

To ensure homogeneity in all participating centres a treatment and postoperative care protocol will be distributed for both the intervention and control groups (online supplemental file 3), in addition to a central cadaver-based TMR course.

#### Control group

The patients in the control group will receive traction neurectomy during the major lower limb amputation, which is the current standard of care in the Netherlands, and this will reduce confounding by the length of the nerve stumps. Ligation or infiltration with a local anaesthetic or alcohol will not be allowed, as we believe this causes significantly more PAP. Amputation technique and nerve handling are carefully documented according to standardised protocols.

#### TMR group

The patients in the TMR group will receive the same amputation technique as the control group, with an additional TMR procedure. TMR will be performed by an experienced nerve surgeon. In the TMR group, each transected nerve identified after amputation is dissected proximally for length. A nerve stimulator is used to identify functional motor nerve branches near the point where the motor branch enters the muscle. The motor nerve branch is transected proximally, and an end-to-end coaptation is performed with the amputated nerve. A major point of criticism in TMR is the size mismatch between the larger amputated nerve and the smaller motor nerve during coaptation. To better understand this factor, a nerve coaptation calibre mismatch score was used in an attempt to standardise the measurement (figure 1).

**Figure 1 F1:**
[figure not shown]
Nerve coaptation calibre mismatch score. Outer circle: amputated nerve; inner circle: motor nerve.

There will not be an expected treatment delay in the TMR group; however, the operation will take approximately 30–90 min longer.^17^ For TMR to be possible in upper leg amputations, an additional incision (around 10 cm) has to be made on the dorsal side of the leg, medial to the sartorius muscle, to coaptate the sciatic nerve. If a tourniquet is used to perform the amputation, the maximum time of inflation is 60 min, after which intraoperative nerve stimulation becomes less reliable due to tourniquet neuropraxia.

### Outcomes

Longitudinal studies show no further improvement of PAP after TMR in amputees after 12 months postoperatively.^15 23 26 27^ Therefore, our follow-up time will be 12 months. Outcomes will be assessed at 2 weeks and at 3, 6, 9 and 12 months via questionnaires (table 1). These will be completed digitally via email, using a pseudo-anonymised data management platform. Patients allocated to the control group who experience significant pain at the end of the study will be offered additional TMR, regardless of amputation level.

**Table 1 T1:** Schedule of enrolment PreventPAP trial

Study period	Enrolment	Allocation	Postallocation						Close-out
Timepoint in Months	0	0	0.5	3	6	9	11	12	12
Enrolment:									
Screening/eligibility criteria	X								
Informed consent	X								
Allocation		X							
Assessment:									
Baseline characteristics	X	X							
Preoperative/intraoperative/postoperative variables	X	X							
Questionnaires:									
NRS RLP and PLP*				X	X	X		X†	
PROMIS Pain Behaviour 7a Short Form^29^				X	X	X		X†	
PROMIS Pain Interference 8a Short Form^29^				X	X	X		X†	
EQ-5D-5L^32^			X	X	X	X		X	
ICAN Pain Sketches^30^				X	X	X		X	
iMCQ and iPCQ^36 37^				X	X	X		X	
PainDetect^31^								X	
HADS^33^								X	
GPE-DV^34^								X	
PLUS-M^35^								X	
Close-out:									
Outcome									X
Medication‡									

* NRS for RLP and PLP will be measured every day for 30 consecutive days at 11 months postamputation.

† Primary endpoint.

‡ Medication will be recorded at the end of the study for the whole study period.

EQ-5D-5L, European Quality of Life - 5 Dimensions - 5 Levels; GPE-DV, Global Perceived Effect - Dutch Version; HADS, Hospital Anxiety and Depression Scale; ICAN, Interdisciplinary Care for Amputee Network; iMCQ, Medical Consumption Questionnaire; iPCQ, Productivity Cost Questionnaire; NRS, Numeric Rating Scale; PLP, phantom limb pain; PLUS-M, Prosthetic Limb Users Survey of Mobility; PROMIS, Patient-Reported Outcomes Measurement Information System; RLP, residual limb pain.

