### Statistical analysis

Continuous variables will be summarised by treatment group using the number of non-missing data points, mean, SD, median and IQR. Categorical and ordinal variables will be summarised by treatment group based on observed frequencies and percentages relative to the total number of non-missing items. To account for the correlation between measurements within the same patient, a repeated measures analysis will be conducted. This will allow us to include all participants with at least a single follow-up measurement. Where appropriate, we will include age, sex and amputation level in our analyses.

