#### Primary study parameter(s)

We selected four co-primary endpoints on the basis of the expected impact of the intervention and relevance for the patients. They are all primarily assessed at 12 months after surgery:

RLP (NRS).PLP (NRS).PROMIS Pain Behaviour Short Form (7 a).PROMIS Pain Interference Short Form (8 a).

These outcomes will be compared between the two treatment groups on the basis of the intention-to-treat principle. The comparisons will be adjusted for age, sex and amputation level, based on clinical relevance. To account for multiple comparisons, we proceed as follows. We start by testing outcomes 1 and 2 at a significance level of 0.025 (two-sided) using the Bonferroni correction. This is the basis of our sample size calculation. Next, we apply a serial gatekeeping procedure:

If both outcomes 1 and 2 reach statistical significance, outcome 3 will be tested at a significance level of 0.05 (two-sided). If outcome 3 reaches statistical significance at that level, outcome 4 will be tested at a significance level of 0.05 (two-sided).If either outcome 1 or 2 reaches statistical significance, outcome 3 will be tested at a significance level of 0.025 (two-sided). If outcome 3 reaches statistical significance at that level, outcome 4 will be tested at a significance level of 0.025 (two-sided).^39^

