#### Cost-effectiveness analysis (CEA)

The economic evaluation will be a trial-based cost-utility analysis (CUA) from a societal perspective (CUA, ie, costs per quality-adjusted life years (QALYs)). Care with and without TMR will be compared with a 1-year time horizon. Estimated societal costs will include hospital (based on study registrations) and other healthcare and productivity costs, using the iMCQ^36^ and iPCQ^37^ at 3, 6, 9 and 12 months. A cost-price analysis will be performed for the TMR. Other healthcare costs will be valued according to the Dutch reference prices whenever possible, including travel costs without discounting (because of the short time horizon). Productivity losses will be valued using the friction-cost method. QALYs will be calculated using the Dutch tariff for the EQ-5D-5L,^32^ at 2 weeks and at 3, 6, 9 and 12 months. Average costs and QALYs will be compared according to ITT, using net-benefit analysis and multiple imputation to account for missing data. Sensitivity analyses will include the cost perspective (healthcare instead of societal) and the utility measure (European Quality of Life visual analogue scale with power-transformation instead of the EQ-5D-5L). If, contrary to expectations, TMR does not deliver better QALYs at lower costs, mathematical extrapolation will be used to perform a threshold analysis on the time horizon.

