### Benefits and risk assessment, group relatedness

The additional risks of performing TMR during an amputation are negligible. TMR can be performed at any level of the lower extremity with a standardised technique. For TMR to be possible in transfemoral and through-knee amputations, an additional sham incision (around 10 cm) must be made on the dorsal side of the leg, medial to the sartorius muscle. To properly blind study participants, this additional incision must also be superficially performed for the transfemoral and through-knee amputations in the control group. In our experience, this will not result in increased postoperative pain or difficulty sitting.

The surgery time for a standard transtibial and transfemoral amputation will be 45–90 min, depending on the surgeon’s experience. The TMR procedure will add 30–90 min to the surgery.^17^ This extra time investment will rely on technical aspects related to the level of amputation and the surgeon’s experience. Although an increase in surgical time of this length is related to a slightly higher risk of infection, Deeyor *et al*^18^ did not find more complications in patients who had acute TMR compared with the standard of care. Deeyor *et al* found a 77% complication rate in the primary TMR group, compared with 87% in the amputation-only group.^18^ There is a small chance of failure of the TMR procedure.^40^ If patients suffer harm from trial participation, the LUMC provides participant insurance for potential financial compensation.

The burden of the study is acceptable, as participation only requires patients to complete several questionnaires at five evaluation time points. This will translate to about 2 min at 2 weeks, 14–21 min at 3, 6 and 9 months and 20–29 min at 12 months postamputation. Additionally, participants will fill out a daily questionnaire consisting of 2 questions about pain for 30 consecutive days at 11 months postamputation. Patients who fail to complete the questionnaires in 2 weeks will receive an automatic reminder and a call from the researcher to promote participant retention.

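### EQ-5D-5L is first taken at 2 weeks and the primary models omit pre-amputation limb pain, so the 1-year QALY has no time-0 utility and some precision is given up

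*Protocol article*

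**What the plan says.** The Outcomes section states that "Outcomes will be assessed at 2 weeks and at 3, 6, 9 and 12 months via questionnaires". In Table 1 neither time-0 column (enrolment, allocation) carries a mark for any questionnaire. EQ-5D-5L is first marked at 0.5 months; the NRS and both PROMIS short forms are first marked at 3 months. The time-0 entries that describe the patient are a row for baseline characteristics and one for "Preoperative/intraoperative/postoperative variables". The contents of these two rows are not listed.

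The section on benefits and risks gives the same schedule independently: "participation only requires patients to complete several questionnaires at five evaluation time points". It times them as follows: "This will translate to about 2 min at 2 weeks, 14–21 min at 3, 6 and 9 months and 20–29 min at 12 months postamputation".

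For the four co-primary outcomes, the Primary study parameter(s) section says "The comparisons will be adjusted for age, sex and amputation level, based on clinical relevance". In the cost-effectiveness section, "QALYs will be calculated using the Dutch tariff for the EQ-5D-5L" at 2 weeks and at 3, 6, 9 and 12 months, over a 1-year horizon. That section gives no time-0 value and no rule for supplying one.

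**The concern.** A QALY over one year is an area under a utility curve that begins at time 0. Here the first point comes 2 weeks after surgery. The 2-week score cannot stand in as a baseline covariate, because it is measured after the randomised treatment and may be affected by it. A chance difference between arms in utility before surgery can therefore be neither seen nor removed.

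Pain in the limb before amputation is a plausible prognostic factor for pain a year later. The Background notes that "persistent nociceptive stimulation in chronic pain may cause various changes in pain physiology, leading to pain sensitisation". That sentence argues for preventing chronic pain rather than treating it later; it does not say that pre-amputation pain predicts 12-month pain. It does make the covariate a natural candidate.

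Randomisation is simple and unstratified, so nothing in the design limits chance imbalance on either variable. An analysis plan can add a covariate later, but it cannot recover a score that was not collected before the operation.

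**Working it through.** **1. Do the places agree?** Yes. Table 1, the Outcomes text, the burden statement and the QALY text all place the first EQ-5D-5L at 2 weeks. Table 1 and the Outcomes text show no pain questionnaire before surgery.

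**2. The plan's own sample size.** Inputs from the Sample size calculation and Primary study parameter(s) sections: difference 2 NRS points, SD 3.5, two-sided alpha 0.025 per outcome, power 90%.

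- n per arm = 2 × (2.241 + 1.282)² × 3.5² / 2² ≈ 76.0, which a strict round-up makes 77. The plan has 76.
- Power at 76 per arm = Φ[(2/3.5) × √(76/2) − 2.241] = Φ(1.281) = 0.90.
- 152/0.94 = 161.7, so 162; 162/0.80 = 202.5, so 203.

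The stated size reproduces, and it uses no baseline covariate.

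**3. Power with pre-amputation pain as covariate.** Let r be its correlation with 12-month NRS, taken as what it adds beyond age, sex and amputation level. The documents give no r, so a range is shown. The residual SD becomes 3.5 × √(1 − r²). Power at 76 per arm is Φ[2 / (3.5√(1 − r²)) × √38 − 2.241]. The number of unadjusted patients giving the same precision is 152/(1 − r²).

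| r (assumed) | Residual SD | Power | Equivalent unadjusted N |
|---|---|---|---|
| 0 | 3.50 | 0.900 | 152 |
| 0.2 | 3.43 | 0.912 | 158 |
| 0.3 | 3.34 | 0.927 | 167 |
| 0.5 | 3.03 | 0.966 | 203 |

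**4. Size of an unlucky imbalance.** With 76 per arm, the standard error of the baseline difference is √(2/76) = 0.162 SD. A 1.96-SE imbalance is 0.318 SD. Without adjustment it moves the NRS difference by r × 3.5 × 0.318: 0.22 points (r = 0.2), 0.33 (r = 0.3) or 0.56 (r = 0.5), against a target of 2 points.

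**5. The missing start of the QALY curve.** The interval is 0.5/12 = 0.0417 year, or 4.2% of the horizon. By the trapezoid rule, a time-0 utility difference d between arms contributes d × 0.0417/2. For assumed d of 0.05 to 0.20 this is 0.001 to 0.004 QALY. The missing area itself is small. What is lost is the use of baseline utility as a covariate for the whole year's QALY.

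**The case against.** **A pain item may already exist.** The contents of the baseline and preoperative rows are not given, and the article condenses a fuller protocol with supplements that are not shown. This stands: a reader might infer that no pre-amputation pain is recorded at all, and the documents do not show that. They show only that no pain questionnaire is scheduled then and that the stated adjustment set leaves such pain out.

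**RLP and PLP have no pre-amputation value.** This also stands. The empty time-0 cells for those two scales are correct. The candidate covariate is a different measure, pain in the limb to be removed, and its correlation with later pain may be modest.

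**The trial already has 90% power, and randomisation deals with imbalance on average.** Correct. A reader might infer bias in the pain or QALY comparison, but a chance imbalance under randomisation is already reflected in the standard error. The sample size stands without the covariate.

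**A time-0 utility rule may sit in a health-economic plan.** It may, and a common value in both arms would define the first 2 weeks. It would not allow adjustment for individual baseline utility.

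Two further inferences fail. A baseline score would not keep patients who die before 3 months in the pain model: of the repeated-measures analysis the plan says "This will allow us to include all participants with at least a single follow-up measurement", and a covariate without an outcome does not meet that condition. Nor can one say that the parallel registry lacks this confounder, since it is to report the same unlisted baseline variables as the trial.

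**Conclusion.** The point holds as a cheap improvement, not as an error that undermines the trial. For EQ-5D-5L the documents are consistent and explicit: there is no time-0 utility, so no baseline-utility adjustment is possible. For pain, the firm statement is narrower: the primary adjustment set omits pre-amputation limb pain, whether or not it is recorded.

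The consequence is lost precision and unadjusted chance imbalance. The gain forgone is slight at r = 0.2 (power 0.91) and material at r = 0.5 (0.97). These figures rest on an assumed r, the planned SD of 3.5 and 76 analysed per arm. No figure is given for the total QALY shift from a baseline utility imbalance, because the documents supply neither the likely imbalance nor how far baseline utility carries over into later utility.

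**What to change.** - **Schedule.** Add EQ-5D-5L to the enrolment column of Table 1 and, if not already captured, one 0–10 NRS for pain in the limb to be amputated. Both are completed after consent and before randomisation. If pain is already recorded, say so and name the item.
- **QALY analysis.** Use the baseline EQ-5D-5L as the time-0 point and as a covariate in the QALY regression. If it cannot be collected, state the time-0 rule (for example a common value in both arms) with a sensitivity analysis.
- **Primary models.** Add pre-amputation limb pain to age, sex and amputation level.
- **Patients already enrolled.** State in advance how their missing baseline values are handled. The economic analysis already plans multiple imputation, which could cover baseline utility; the primary models need their own rule.

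The cost is a small amendment and an estimated 2 to 3 minutes per patient at consent. The plan's 2-week questionnaire, which Table 1 shows to be EQ-5D-5L alone, is put at about 2 minutes. The downsides are that extra burden in a semiacute setting and the missing baseline values for patients already enrolled.
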